## Abstract

**Background:**

The effects of a regular and graduated walking program as a stand-alone intervention for individuals in long-term care are unclear. Exercise and fall prevention programs typically studied in long-term care settings tend to involve more than one exercise mode, such as a combination of balance, aerobic, strengthening, and flexibility exercises; and, measures do not always include mental health symptoms and behaviors, although these may be of even greater significance than physical outcomes.

**Methods/design:**

We are randomly assigning residents of long-term care facilities into one of three intervention groups: (1) *Usual Care Group* - individuals receive care as usual within their long-term care unit; (2) *Interpersonal Interaction Group* - individuals receive a comparable amount of one-on-one stationary interpersonal interaction time with study personnel administering the walking program; and, (3) *Walking Program Group* – individuals participate in a supervised, progressive walking program five days per week, for up to half an hour per day. Assessments completed at baseline, 2 and 4 months during intervention, and 2 and 4 months post-intervention include: gait parameters using the GAITRite® computerized system, grip strength, the Berg Balance Scale, the Senior Fitness Test, the Older Adult Resource Services Physical Activities of Daily Living, the Geriatric Depression Scale Short Form, the Cornell Scale for Depression in Dementia, the Revised Memory and Behavior Problems Checklist, the Short Portable Mental Status Questionnaire, the Coloured Analogue Scale, pain assessment scales, and the number and nature of falls. Sophisticated data analytic procedures taking into account both the longitudinal nature of the data and the potential for missing data points due to attrition, will be employed.

**Discussion:**

Residents in long-term care have a very high number of comorbidities including physical, mental health, and cognitive. The presence of dementia in particular makes standardized research protocols difficult to follow, and staff shortages, along with inconsistencies related to shift changes may impact on the accuracy of caregiver-rated assessment scales. Practical challenges to data collection validity and maintenance of inter-rater reliability due to the large number of research staff required to implement the interventions at multiple sites are also posed.

**Trial registration:**

ClinicalTrials.gov NCT01277809

## Background

Routine physical activity, as an essential component of healthy and successful aging, is a means of maintaining mobility and functional abilities in aging adults [1-3]. A common challenge for long-term care (LTC) residents is decreased mobility, the ability to move independently within one’s environment [4], or immobility, with an estimated 89% of nursing home residents experiencing some level of mobility limitation [5]. Decreased mobility and immobility are associated with a variety of physical and psychosocial impairments, including depression, anxiety, feelings of isolation, activity limitations, and complications in almost every body organ system [6-10]. In addition, decreased mobility and immobility lead to a devastating spiral of further disability and health problems. While it is thought that decreased mobility or immobility are natural consequences of aging, researchers have found that frail older adults have a much greater potential for increased mobility, and physical, psychological and functional improvements than previously thought possible [11-14].

Clinical trials of exercise interventions, including strength, endurance, balance and functional training, or combination training, in LTC settings have led to significant positive effects on health outcomes [11,12,15-19]. Interventions that are both efficient and effective in maximizing resident’s mobility and functional abilities are essential, particularly in chronic care settings. However, sustainable approaches to incorporating physical activity or mobility interventions that are acceptable to both residents and staff, and that can be inclusive of a large proportion of those living in LTC facilities have not yet been identified [20]. Walking, as an intervention, is ideal in its simplicity as a means of improving mobility, strength, and endurance, and in its ability to be integrated into daily care routines. Although limited by non-random samples and unblinded outcome measurement, earlier studies of walking programs have been found to be beneficial in improving walking endurance [21], ambulation status [22], and urinary incontinence [23]. Combined walking and talking interventions have also been found to be beneficial. Improved communication performance in LTC residents who participated in a walking and talking program compared to those who engaged in talking alone has been reported [24]. Tappen, Roach, Applegate and Stowell (2000) compared combined walking (30 minutes of self-paced assisted walking three times per weeks for 16 weeks) and talking (30 minutes of conversation) to walking alone and talking alone. Pre-test and post-test measurement found less decline in the distance walked in six minutes in the combined treatment group – 2.5% decline versus 18.8% decline (talking group) and 20.7% decline (walking group) [25]. Building on prior work, Cott and colleagues (2002) compared walking and talking in pairs (30 minutes 5 times per week for 16 weeks) to talking alone (conversation in pairs) and no-intervention. The walking and talking intervention did not produce statistically significant differences in communication, ambulation or functional status. The authors noted that for those with moderate to severe dementia, the dual task of walking and talking with another resident (“pair walking, talking”) may be too much stimulation, leading to multiple stops and starts of the walk and may have resulted in insufficient walking [26]. In summary, the extent of the research-to-date examining the effects of walking programs is equivocal and limited. Previous studies have focused on selective outcome measures and have not examined the effects of a walking program on falls, pain, psychosocial function and behavior.

In this paper, we describe a study protocol assessing the effectiveness of an individualized, progressive, walking program (which inevitably involves human interaction) compared to usual care and to a human interaction condition (no walking) in individuals residing in long-term care facilities. Our study protocol addresses methodological limitations of previous LTC walking studies; specifically, we: 1) have included a broader array of physical, physiological and psychosocial outcome measures, including measures of strength, balance, flexibility, blood pressure, heart rate, weight, height (total and knee-floor), waist, upper arm and calf circumference, pain, activities of daily living (ADL), behaviour, falls, hospitalizations, depression, cognition, psychotropic medication use; 2) will examine gait speed and gait characteristics using a computerized system; and, 3) are ensuring that participants are receiving adequate Vitamin D, 1000 IU per day, based on most recent recommendations regarding the use of Vitamin D in older persons residing in LTC settings [27].

## Methods/Design

### Design

This study is a prospective, randomized, three-group design with multiple dependent variables. The three groups include: (1) Participants receiving care as usual (*Usual Care Group*); (2) Participants receiving stationary 1:1 interaction time with research personnel in order to control for the interpersonal interaction (*Interpersonal Interaction Group*); and, (3) Participants engaging in an individualized, progressive, one-to-one supervised walking program five days per week (*Walking Program Group*).

### Ethics

The study has been approved by all necessary research ethics boards (i.e., university, as well as health region).

### Target population, inclusion and exclusion criteria

Participants over the age of 60 are being recruited from long-term care facilities. To be included in the study, residents must be able to follow simple instructions, must be able to ambulate with or without a walking aid for at least 10 metres, must be available Monday-Friday for interventions and be willing to participate in a 5-day per week walking program over a 4-month period. Residents who have experienced a recent cardiovascular event (within past 6 months) or have severe, mobility limiting arthritis, cardiac instability, a severe, mobility limiting vestibular disorder, uncontrolled hypertension, uncontrolled epilepsy, a recent fracture (past 4 months), who are unable to satisfactorily comply with the protocol requirements, who have had a recent admission into an acute care facility (past 4 months), who are scheduled for surgery or hospitalization in the next 6 months or who are participating in another regular exercise program (half an hour or more, three or more times per week ) aimed at improving balance or strength will be excluded from the study.

### Sample size

Sample size calculations assumed a moderate standardized effect size of 0.40 [28], a small value for the intra-class correlation (i.e., the proportion of variation accounted for by LTC units) of 0.05, and α = .05, power = .80. Sample size calculations determined that a sample size of 129 total participants will provide ample power for repeated measures analyses [29]. A balanced design will be adopted, with equal numbers of participants in each group. We will collect data from an additional 50 participants in order to account for attrition due to refusal or inability to continue with the protocol. As well, morbidity and mortality may account for some attrition.

### Recruitment

The investigators will meet with each of the LTC facilities’ administrators and staff to inform them of the study, inclusion and exclusion criteria, and study procedures and interventions. Staff is asked to identify potential/eligible participants who are then approached by research assistants and asked if they wish to participate in the study. If the potential participant agrees to participate, this is considered to be assent, regardless of capacity for full, informed consent. The research assistant then explains the study, asking the participant questions to assess full understanding of the protocol including potential benefits and adverse effects. If the participant clearly understands the protocol, he/she will is invited to sign a full consent form. If the participant does not have full understanding of the protocol, or the capacity of the subject is unclear, the research assistant asks permission to contact the substitute decision-maker (SDM) who normally consents to health care decisions. If the participant declines, he/she will not be entered into the study. If the participant agrees, the SDM is approached and the protocol is explained in detail. The consent form is signed by only the SDM when the participant clearly has no capacity, and by both the participant and the substitute decision-maker when capacity is unclear or diminished

### Procedures

After completing informed consent to participate in the study (or proxy consent by the appropriate SDM), all participants regardless of group will undergo a baseline assessment (see outcome measures section) conducted by trained study personnel prior to group allocation. Prior to enrolment in the specific study arm, family physicians are asked to optimize vitamin D levels, which will generally require obtaining vitamin D levels and prescribing 1,000 IU Vitamin D (if the participant is not already taking 1,000 IU or more) to control for potential influences on our study outcomes, and to be consistent with current recommendations [27]. Adherence with Vitamin D recommendations is monitored and reasons for intake problems are recorded.

Physical measures including respiratory rate, lying (after three to five minutes) and standing (after one minute) blood pressure, heart rate, as well as full height, knee-floor height, waist and calf circumference and weight are also collected at the beginning of the study, and except for height, measured also at week 8, week 16, week 24 and week 32, and whenever a medical concern arises. All adverse events (including falls, hospitalizations and surgeries) charted in nurses progress notes are collected, as are most recent full Resident Assessment Instrument-Minimum Data Set (RAI-MDS) and RAI-MDS updates, and the full, monthly medication administration record.

A licensed physiotherapist will assess the participant for fall risk and assign a visual analogue risk score ranging from negligible fall risk to highest fall risk, commenting on the reasons for the risk score assigned.

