### Intervention

Participants within each facility are randomly assigned to one of three intervention groups. The intervention period is four months. Participants in the control group receive the usual care of their LTC unit throughout the four month time period, with the exception of scheduled outcome assessments. Participants in the Interpersonal Interaction group receive an approximately equivalent interpersonal interaction time (up to 30 minutes per day, five days per week) with research personnel as those in the Walking Program group. The interaction time occurs with the participant stationary. The participants in the Walking Program group receive an individualized, progressive, one-to-one supervised walking program provided by study personnel and supervised by a licensed physiotherapist. Each participant in this group walks once per day (up to half an hour), five days per week. The initial distance walked is initially determined for each individual based on how far the person can ambulate before visibly becoming fatigued or short of breath, reporting pain or requesting to sit down or rest. The distance walked and the intensity of the walking program during the four month period is gradually increased, as tolerated by the individual.

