### Outcome measures

Outcome measures are completed at baseline. Re-assessment occurs after two months and four months of the intervention period, and at two and four months after the intervention period. The assessment of the outcome measures will be conducted by study personnel who are blind with respect to group allocation. The outcome measures include:

(1) Seniors Fitness Test (SFT) [30]. The SFT is a six-item battery, with demonstrated intra-rater and test-retest reliability and validity in older adults [30]. The SFT includes measures of dynamic upper (arm curls) and lower extremity strength (30-second sit-to-stand) and flexibility, aerobic endurance (2-minute step test), and mobility (8-ft walk test) [30].

(2) Berg Balance Scale (BBS). The BBS, a 14-item battery that assess a person's ability to safely perform several common daily living tasks, and is widely used as a measure of balance performance and fall risk assessment [31-33]. Performance on each item is rated on a scale from 0 (cannot perform the task) to 4 (normal performance of the task) and the maximum obtainable score is 56. The BBS has been reported to have excellent interrater and intrarater reliability and concurrent and discriminant validity [34].

(3) Grip strength. Grip strength is a reliable measurement when standardised methods and calibrated equipment are used, independent of evaluator or type of dynamometer, [35] and has been found to be a powerful predictor of disability, morbidity and mortality [36-38]. We will measure grip strength using a hand-held dynamometer using standard testing procedures. Three maximal repetitions (with 30 second rest between attempts) will be recorded for the dominant and non-dominant hand.

(4) Older American Resource Services (OARS) Activities of Daily Living Scale. The OARS is a brief, valid, and reliable instrument that is used as a clinical assessment of functional status [39]. The OARS ADL scale includes seven basic ADL items (eating, dressing and undressing, grooming, walking, getting in and out of bed, bathing, and continence), and seven instrumental ADL items (using the telephone, travel, shopping, meal preparation, housework, taking medicine, and management of finances) [39]. We will record the scores for the BADL items.

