### Data analysis

We hypothesize that participants taking part in the walking program will demonstrate maximal benefits compared to the no treatment control group (usual care) and the participants receiving only social interaction. We hypothesize that benefits of the walking program will include decreased fall rates, and improved balance, endurance, strength, mood, behaviour, activities of daily living and quality of life indices. As research has found that pleasant activities improve resident mood [54], we also hypothesize that participants in the social interaction group will demonstrate improvements in mood and other indices of quality of life.

The data will be analyzed using a random-effects multiple regression model [55]. The between-subjects factor will be condition (i.e., treatment and two control conditions). A random intercept for time (i.e., 5 measurement occasions) will be included to account for within-subject variation due to the repeated measurements. We will also evaluate model fit when a random slope for time is included in the model. Model fit will also be evaluated when the time x group interaction is included in the model. Additional covariates that may be included in the model are clinical measures from the RAI-MDS, such as the presence of comorbid conditions. Evaluation of model fit will be conducted using likelihood ratio tests and the Aikake Information Criterion [55]. Proportions of participants in the number of fall categories (e.g., non-faller, one-time faller, multiple faller) will be assessed using Pearson’s chi-square statistics.

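### The falls comparison is fixed as an unadjusted chi-square test, which cannot use the baseline fall-risk information the trial already collects; the loss is precision, not validity

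*Protocol article*

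**What the plan says.** **Fall-risk information collected.** Under Procedures: "A licensed physiotherapist will assess the participant for fall risk and assign a visual analogue risk score", with comments on the reasons. That sentence gives no time for the scoring. The same section places the "baseline assessment (see outcome measures section) conducted by trained study personnel prior to group allocation". The outcome measures section does not list the physiotherapist's score, but it does list the Berg Balance Scale, described as "widely used as a measure of balance performance and fall risk assessment". A Berg score before allocation is therefore part of the plan, while the timing of the visual analogue score is open.

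**Falls hypothesis.** Data analysis expects that "benefits of the walking program will include decreased fall rates".

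**Falls analysis.** "Proportions of participants in the number of fall categories (e.g., non-faller, one-time faller, multiple faller) will be assessed using" Pearson's chi-square statistics. No covariate, stratum or length of follow-up is mentioned for this comparison.

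**Covariates elsewhere.** "Additional covariates that may be included in the model are clinical measures from the RAI-MDS, such as the presence of comorbid conditions". This sentence concerns the random-effects regression model for the repeated measures, not the falls test.

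**The concern.** A reduction in falls is a stated hypothesis of the trial, and the arms are small. Each resident's baseline fall risk is likely to explain part of who falls, and the trial measures that risk. A chi-square test on a table of arm by fall category leaves the information unused. At stake are the chance of detecting a real difference in falls, and how convincingly the result can be read if one arm happens to start at higher risk than another.

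This is more than a detail left for later. The article names the test, and the named test cannot be adjusted.

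**Working it through.** **Inputs from the Protocol article.** Sample size gives 129 participants in equal groups, so 129 / 3 = 43 per arm. With the 50 added for attrition the total is 179, and 179 / 3 is about 60 per arm. Intervention states that individuals are randomised within facility. The sample size is set for the repeated measures analyses; the article gives no power for falls, so there is no falls figure to reproduce. Only the arm size is used below.

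**Assumptions not in the documents.** The fall frequency, the prognostic strength of the risk measure and the treatment effect are all assumed, as stated in each step.

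**Step 1: chance imbalance.** In SD units, the standard error of the difference in mean baseline score between two arms is sqrt(2/n).

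| | 43 per arm | about 60 per arm |
|---|---|---|
| Standard error | sqrt(2/43) = 0.216 | sqrt(2/59.67) = 0.183 |
| 95% range for one pair (1.96 × SE) | ±0.42 SD | ±0.36 SD |
| One given pair differs by 0.3 SD or more | 16% | 10% |
| Some pair of the three differs by more than 0.4 SD (simulated) | 15% | 7% |

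These figures follow from arm size alone and hold for any baseline variable. For scale, suppose the fall rate rises 1.5- to 2.5-fold per SD. A 0.3 SD gap would then by itself give an apparent rate ratio of 1.5^0.3 = 1.13 to 2.5^0.3 = 1.32, or the inverse.

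**Step 2: is the unadjusted test valid?** I simulated trials of 43 per arm with no treatment effect, a mean of 0.6 falls per resident, three fall categories and 4,000 trials per case.

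| Log fall rate per SD of risk | Type I error, all trials | Type I error, trials with some pair more than 0.4 SD apart |
|---|---|---|
| 0.3 | 4.3% | 4.1% |
| 0.5 | 5.1% | 7.3% |
| 0.8 | 4.6% | 9.3% |

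Over all randomisations the test keeps its level. Only within the roughly 15% of trials that happen to be imbalanced does the false-positive rate rise, and then only when the risk measure is a fairly strong predictor.

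**Step 3: what does adjustment gain?** I simulated faller versus non-faller with 43 per arm and 1,000 trials per case. The probability of falling at the mean score was 1/(1 + e^0.2) = 45%, and the odds ratio for walking was 0.33. The chi-square test was set against a likelihood-ratio test from a logistic model adjusted for the score.

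| Log-odds per SD of risk | Chi-square power | Adjusted power | Gain | Null rejection, chi-square / adjusted |
|---|---|---|---|---|
| 0.5 | 62.0% | 67.3% | 5.3 points | 5.2% / 6.4% |
| 1.0 | 52.5% | 61.3% | 8.8 points | 5.6% / 5.5% |

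The simulation error of a 5% rejection rate is sqrt(0.05 × 0.95 / 1000) = 0.7 points. In the first row the adjusted test rejects slightly more often under the null, so part of the 5.3 points may not be real gain. The second row does not have that difficulty.

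**The case against.** The strongest reply is that nothing here is an error. Allocation is random, the error rate of the test already covers chance imbalance, and adjusting for a prognostic covariate is a preference. The part about validity stands, and Step 2 confirms it. What remains is an avoidable loss of power on a stated hypothesis.

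Several stronger readings are tempting, and the documents do not support them:

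- **That the falls comparison is biased or invalid.** It is not; see Step 2.
- **That the plan discards the physiotherapist's score.** The article mentions no use for it, but a condensed article may leave that to the full protocol or the statistical analysis plan. Silence is not a decision to ignore it.
- **That the score is contaminated by knowledge of the arm.** The walking programme is "provided by study personnel and supervised by a licensed physiotherapist", so a reader might infer that the same person scores risk after allocation. The article says neither that it is the same person nor that scoring follows allocation. The missing time matters only because a score assigned after allocation could not serve as a baseline covariate.
- **That this score is the only fall-risk measure.** The Berg score is taken before allocation, so balance can be checked and adjustment made without the visual analogue score. Its availability does not cure the problem, because the chi-square test cannot use it either.

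It is also fair to say that the size of the gain depends wholly on assumed prognostic strength and an assumed large effect.

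**Conclusion.** The point holds as a matter of efficiency and interpretability. The article commits the falls comparison to a test that cannot take baseline fall risk into account, although the trial collects such information and hypothesises fewer falls. The cost is about 5 to 9 percentage points of power at 43 per arm, given an odds ratio of 0.33, 45% fallers at average risk and a log-odds of 0.5 to 1.0 per SD. A weaker predictor would gain less. In addition, about 15% of trials of this size would have some pair of arms more than 0.4 SD apart in baseline risk (7% at about 60 per arm), and an unadjusted result would then be open to dispute. The type I error over all randomisations is sound. The change is worth making because it is nearly free, not because the present test would give a wrong answer.

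**What to change.** In Data analysis, make the main falls comparison a regression with arm as factor and baseline Berg score as a prespecified continuous covariate. Two forms would serve: ordinal logistic regression on the fall categories, or a count model with each resident's follow-up time as exposure. The second matches the hypothesis about fall rates more closely and allows for unequal follow-up. Keep the Pearson chi-square as a supportive analysis.

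The physiotherapist's score may be used in place of Berg provided it is assigned before allocation. If so, Procedures should say that it is assigned then. If that cannot be assured, use Berg.

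I would not rely on a table of falls by arm within low, middle and high risk: 43 / 3 is about 14 residents per arm and level, too few to show where falls concentrate.

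The cost is some added analysis work and model assumptions in place of a simple test. An adjusted odds ratio from the logistic form is also not directly comparable with the unadjusted one, so the report should label which is which. No data, visits or staff are added.
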